### 3. STUDY DESIGN

This is a randomized placebo-controlled trial in which 100 consented adults with chronic low back pain (CLBP) will be randomized to 6 weeks of twice a week sessions with verum acupuncture (VA) or sham/placebo-acupuncture (PA). Participants and researchers will be blind to treatment assignment. Treatment providers will not (and cannot) be masked to treatment assignment.

Timeline: Eligible participants will be invited for a baseline visit. Since the focus of this study is prediction, extensive collection of baseline characteristics, including physical (vital signs and heart rate variability, physical exam), psychological (questionnaires), and QST measures will be collected around and at the time of the baseline visit. Approximately 1 week after the baseline visit, the participant will enter

a 6-week treatment phase, during which they will be randomized to VA or PA. (See Section 4.3.2. for details of randomization). The Post-Treatment Visit will take place 1 to 2 weeks after the last treatment visit. Participants will then be followed up and assessed at 3, 6 and 12 months after treatment ends. Thus, participants will be in the project for a total of approximately 12 months.

Location: The treatments will be provided at 7 sites: our laboratory (SNAPL) where our main acupuncturist ([name]) will be providing services to patients located on and near the Peninsula; as well as 6 other acupuncture clinics located in the greater San Francisco Bay Area (SF, South and East Bay). The baseline and post-treatment visit will take place at our laboratory, SNAPL (Systems Neuroscience and Pain Laboratory) at the Stanford Division of Pain.

Interventions: The interventions, verum (electro) acupuncture (VA) and sham/placebo ('electro') acupuncture (PA), are described in detailed in Section 5 (Project Interventions). Interventions will be provided at no charge to participants.

Primary outcomes: a) Change in Pain Intensity measured by the PROMIS Pain Intensity Instrument administered at the pre-treatment and post-treatment visit. . b) a responder is defined as one who experiences  $\geq 10\%$  reduction in the T-score (1 standard deviation) of the full instrument, or  $\geq 1$  point decrease in the 5-point Likert Scale of the mean pain intensity question in the PROMIS Pain Intensity Instrument.

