### 4.1 Inclusion Criteria

Participants must meet all of the following inclusion criteria in order to be enrolled in the project.

- Males and females, ages 21-65
- English fluency
- Have had chronic low back pain for at least 6 months:

Definition of Chronic Low Back Pain (cLBP)—criteria from the NIH Task Force for cLBP

- Chronicity: cLBP "defined as a back pain problem that has persisted at least 3 months and has resulted in pain on at least half the days in the past 6 months."
  - Location: "between the lower posterior margin of the rib cage and the horizontal gluteal fold."
- Average pain over the last month  $\geq 4/10$  for initial eligibility

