|               | Demographics                             | X               |                                                                                                    |              |       |       |             |       |        |               |                     |
|               | Pain Intensity (30 d) (NRS)              | X               |                                                                                                    |              |       |       |             |       |        |               | X                   |
|               | Pain Intensity (7 d) (NRS) – to be added |                 |                                                                                                    | X            |       |       |             |       |        | X             |                     |
|               | BodyMap                                  | X               |                                                                                                    | X            |       |       |             |       |        | X             | X                   |
|               | NIH Dataset                              | X               |                                                                                                    |              |       |       |             |       |        |               |                     |
|               | STartBACK Tool                           | X               |                                                                                                    |              |       |       |             |       |        |               |                     |
|               | Medical History                          | X               |                                                                                                    |              |       |       |             |       |        |               |                     |
|               | Medication List                          | X               |                                                                                                    |              |       |       |             |       |        |               |                     |

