Online Follow-Up. Participants will complete online assessments at 3, and 6 and 12 months post-treatment. These assessments will include a limited dataset out of the questionnaires that the participant completed at their Baseline Visit (RMDQ and mean pain intensity). Specifically, these questionnaires are scheduled to reach the participant at 3, 6, and 12 months measured from the LAST day of intervention. Our automatic survey invitation is programmed such that, if the participant has not responded, the questionnaire will be sent 3 more times weekly until a response is entered.

In order to increase the capture of long-range data, the research team will also reach out via email or phone to the participants who have missed all 4 email reminders. The windows for completions are: up to 6 months for the 12-month survey, up to 3 months for the 6-month survey and up to 1 month for the 3 month survey. In order to find the balance between maximizing data capture and accuracy of recall, for the participants who are outside their window, we ask them to recall the approximate average back pain intensity at 3, 6 or 12 months after their last study intervention.

Debriefing. On the post-treatment assessment visit, all participants will be debriefed by RC the research team. The PI or the RC will only unblind the participant AFTER all assessments are completed at the post-treatment visit.

The table below summarizes the visits for the project.

| Week Number* | Visit                             | Events                                                                                                                    |
|--------------|-----------------------------------|---------------------------------------------------------------------------------------------------------------------------|
| Week -1      | Screening Visit                   | Informed consent, eligibility determination/enrollment, questionnaires, physical exam, HRV/QST, daily and weekly tracking |
| Week 0       | Pre-treatment/baseline assessment | More questionnaires, HRV/QST, randomization                                                                               |
| Week 1       | Treatment sessions 1 and 2        | Treatment per protocol                                                                                                    |

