## 9.5 Outcomes

### 9.5.1 Primary Outcome

**Primary outcome:** Change in Pain Intensity measured by the T-scores computed from the full PROMIS Pain Intensity Instrument administered at the pre-treatment and post-treatment visit.

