### 9.5.2 Secondary Outcomes

**Secondary outcomes:** a) percent pain reduction at 6 and 12 months from baseline; b) percent change in physical function, measured by RMDQ or the pain interference instrument from PROMIS at the post-treatment visit, and at 3, 6 and 12 months from baseline. C) percent change in pain intensity measured by the 11-point NRS at both the pre- and post- treatment visit.

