1516 immediately after treatments. The primary analyses will be the computation of mean-squared  
1517 prediction error from a multivariate regression model, as well as the use of Lasso and cross-validation to  
1518 improve and validate the predictive model with TS. The second objective will be to quantify the  
1519 association between TS and pain reduction immediately after treatments (ie secondary outcome is the  
1520 same as the primary outcome, pain reduction immediately after treatments). The secondary analyses  
1521 will be a) computation of the correlation coefficient between baseline TS and pain reduction and b)  
1522 estimation of the regression coefficient and 95% confidence intervals between baseline TS and pain  
1523 reduction in a multivariate regression model taking TS and other baseline variables into account.

1524 The same analyses will be applied to pressure pain threshold and widespread pain. Realizing that pain  
1525 reduction may not be normally distributed and that the assumed linear regression model may not be  
1526 appropriate, we will repeat the above analysis using a conservative, semi-parametric transformation  
1527 model. We will perform the parallel logistic analysis with dichotomized pain-reduction (responder vs  
1528 non-responder) as the binary dependent variable of interest. We will perform similar analyses for  
1529 widespread pain. Finally, we will repeat the above using pain reduction at 6 months post-treatment as  
1530 our outcome variable.

1531 **Aim 2. Explore the predictive relationship and the association between descending pain modulatory**  
1532 **measures and clinical response to acupuncture.**

1533 **Planned analysis:** the statistical plan for Aim 2 is almost identical to that of Aim 1 except, we replace  
1534 baseline factors of TS, pressure pain threshold and widespread pain, with baseline CPM, pain  
1535 catastrophizing, coping effectiveness and self-efficacy. In summary, the primary objective will be to assess  
1536 the predictiveness of baseline descending pain modulatory factors (CPM, pain catastrophizing, coping  
1537 effectiveness and self-efficacy for pain management) to pain reduction; and the primary outcome of  
1538 pain reduction will be the difference in pain between baseline and immediately after treatments. The  
1539 primary analyses will be the computation of mean-squared prediction error from a multivariate  

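### The 6- and 12-month pain analyses cannot use the T-score or the defined responder, and the follow-up scale's only scheduled earlier value is the screening score used for eligibility

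*Protocol*

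**What the plan says.** Section 9.5.1 defines the primary outcome as "Change in Pain Intensity measured by the T-scores computed from the full PROMIS Pain Intensity Instrument", taken at the pre- and post-treatment visits. Section 3 calls a participant a responder if the T-score falls by at least 10%, or if there is at least a 1-"point decrease in the 5-point Likert Scale of the mean pain intensity question in the PROMIS Pain Intensity Instrument". Both limbs are PROMIS quantities.

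For Aim 1, section 9.6 sets out correlations, regressions, an interaction with arm, lasso with cross-validation and a transformation model, and then: "We will perform the parallel logistic analysis with dichotomized pain-reduction (responder vs" non-responder). It closes with "Finally, we will repeat the above using pain reduction at 6 months post-treatment as" the outcome variable. Aim 2 follows almost the same plan, and section 1.2 carries long-term relief into all three aims. Section 9.5.2 lists "percent pain reduction at 6 and 12 months from baseline" without naming an instrument or saying which value is the baseline.

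In the schedule in 6.1, the row "Pain Intensity (30 d) (NRS") is marked at screening and at the 3-, 6- and 12-month follow-ups only. Section 6.2.5 describes the follow-up set as a subset of what the "participant completed at their Baseline Visit (RMDQ and mean pain intensity"). Section 4.1 uses "Average pain over the last month" of at least 4/10 as an entry criterion.

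**The concern.** Two things do not fit together. First, 9.6 asks for the responder model again at 6 months, but the instrument that defines a responder is not given at 6 months. Second, percent reduction from baseline needs a baseline on the follow-up scale. The schedule offers only the screening score for that, while 6.2.5 implies a value from the baseline visit.

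The first gap leaves a stated analysis without a definition. The second leaves the analyst to choose a baseline after the fact, and the one available for everybody is the score that decided who entered. Starting from a score selected to be high makes a later score look lower on average even if nothing has changed. In a percent-reduction or responder summary, that reads as lasting relief.

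**Working it through.** **Step 1: what is collected when (6.1, with 4.3.1).**

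| Measure | Screening | Pre-treatment | Post-treatment | 3, 6, 12 months |
|---|---|---|---|---|
| PROMIS packet (T-score and Likert mean-pain item) | no | yes | yes | no |
| 7-day NRS | no | yes | yes | no |
| 30-day NRS | yes | only if re-asked under 4.3.1 | no | yes |

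No T-score and no Likert item exist at 6 or 12 months, so both limbs of the responder rule are unavailable for all participants. The 7-day NRS has a pre-treatment value but no follow-up value. Only the 30-day NRS spans both ends, and its scheduled start is screening.

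**Step 2: how old the screening score can be.** The usual gap from screening to the pre-treatment visit is 1 to 2 weeks (6.2.2). Under 4.3.1, 30-day pain is re-asked at the pre-treatment visit for returns at 1 to 3 and 3 to 6 months, and the whole screening visit is repeated after 6 months. A score that has not been refreshed is therefore at most about 1 month old at that visit. Some participants will have two candidate baselines and others one, and the protocol does not say which counts.

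**Step 3: regression to the mean from the entry rule.** The protocol gives no NRS SD or reliability, so these inputs are assumptions: population mean μ from 4.5 to 5.5, SD σ from 1.5 to 2, and correlation ρ between two occasions from 0.5 to 0.8. Scores are taken as normal, entry requires a score of at least 4, and there is no true change.

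- a = (4 − μ)/σ and λ = φ(a)/(1 − Φ(a))
- mean among those selected = μ + σλ
- expected fall at the next occasion = (1 − ρ)σλ

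Smallest case (μ 5.5, σ 1.5, ρ 0.8): a = −1, λ = 0.2876, fall = 0.2 × 1.5 × 0.2876 = 0.09 points. The selected mean is 5.5 + 1.5 × 0.2876 = 5.93, so the fall is 1.5%.

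Largest case (μ 4.5, σ 2, ρ 0.5): a = −0.25, λ = 0.6458, fall = 0.5 × 2 × 0.6458 = 0.65 points. The selected mean is 4.5 + 2 × 0.6458 = 5.79, so the fall is 11%.

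**Step 4: chance responders.** No NRS responder rule is in force. For illustration, take a fall of at least 30% or at least 2 points, the NRS rule that the revision history describes as formerly used. Simulating the same grid with no true change:

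- from the screening score, 3.6% to 28.2% meet the rule;
- from a fresh pre-treatment score in the same selected people, 2.8% to 20.5% still meet it.

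The part due to selection is the difference: 3.6 − 2.8 = 0.8 points at the low end and 28.2 − 20.5 = 7.7 points at the high end. The rest is ordinary measurement noise.

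**The case against.** The strongest reply is that 9.6 does not say T-score at 6 months. It substitutes 6-month pain reduction as the outcome, and 9.5.2 speaks only of percent pain reduction. The correlations, regressions, interaction, lasso and transformation model can all be run on the NRS, and the derivation of a secondary endpoint may be left to an analysis plan. This stands for the continuous analyses. It does not rescue the responder model, because the only definition in force is tied to PROMIS, and an analysis plan cannot supply data that were not scheduled.

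A reader might infer that there is no like-for-like baseline at all. The documents do not support that: the screening score is the same item, scale and recall period as the follow-up score. A reader might also infer that the baseline could be six months out of date. The re-asking rule in 4.3.1 rules that out.

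It is also fair to say that the aims concern predictor associations and their interaction with arm, and that the Aim 1 regression already lists baseline pain as a covariate. Regression to the mean should fall on both randomised arms alike. That largely spares the verum-sham contrast, but not percent reductions or responder rates reported within an arm.

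Finally, a 30-day item re-asked 1 to 2 weeks after screening shares 23 to 16 of its 30 days with the first answer, so a new value reduces the selection effect without removing it. That also stands.

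**Conclusion.** The point holds in a limited form. It is certain from the documents that neither the T-score change nor the responder as defined can be obtained at 6 or 12 months, and that 6.1 and 6.2.5 disagree on when the follow-up pain item was first asked. A same-instrument change from screening remains available, but it starts from a score used for selection. Under the assumed inputs this alone produces a mean fall of about 0.1 to 0.65 points (1.5% to 11%).

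It would be wrong to read the whole chance-responder figure as a product of the screening baseline: most of it would appear with any baseline. It would also be wrong to infer a biased comparison between arms. The primary outcome, which has matched pre- and post-treatment T-scores, is untouched. This is a correction that should be made to the secondary, long-term analyses.

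**What to change.** In 9.5.2 and 9.6, define the 6- and 12-month pain outcome on the 30-day NRS, and give it its own NRS responder rule in place of the PROMIS-based one.

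Ask the 30-day NRS of every participant at the pre-treatment visit, as 4.3.1 already does for returns at 1 to 6 months. Name that value as the baseline for the long-term analyses, and bring 6.1 and 6.2.5 into agreement.

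Keep baseline NRS as a covariate in the long-term models. For participants already enrolled without a pre-treatment value, use the screening score and flag it.

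The cost is one extra question and some analysis wording. The downside is two sources of baseline within one trial, so a sensitivity analysis should check whether the results depend on the source, for example by using the screening score for everyone.

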## 1575 10. DATA COLLECTION AND QUALITY ASSURANCE

### 1576 10.1 Data Collection Forms

1577 All questionnaires will be completed by participants in the REDCap Database. If some questionnaires  
1578 have to be collected on paper due to unforeseen circumstances, the forms will be stored as source data  
1579 and a member of the research team will enter the data into the REDCap database.

1580 Participants will complete majority of the questionnaires associated with the pre- and post-treatment  
1581 visits on-site. To ease participant's burden during their onsite visit, we will send longer questionnaires  
1582 and those with relatively less predictive power based on prior studies via weblinks such that participants  
1583 can complete them at the comfort of their home. All follow-up questionnaires will be completed online  
1584 by the participants at home.

1585 The research team will fill out the majority of the CRF's and keep these along with the Phone Screen as  
1586 source data. The acupuncturists will fill out a CRF for initial intake and a CRF for each acupuncture  
1587 session to record details of the treatment.

1588 All participants will be identified by a unique project ID number on their corresponding data and case  
1589 report forms and will not be identified by their name. All CRFs will be stored in binders identified by the  
1590 Participant ID number and stored in locked cabinets. All staff will receive training on completing CRFs  
1591 appropriately, reviewing CRFs for completeness, and maintaining participant confidentiality.

1592 **10.2 Data Management**

1593 The PI and the RC will be responsible for collecting data but both will be blinded to treatment  
1594 assignment. Most importantly, PRIOR to analysis, the lab manager or his associates who are not involved  
1595 with the current study will de-identified key baseline and outcome data and send these to the PI, RC and  
1596 steering committee for analyses.

1597 **10.3 Quality Assurance**

1598 **10.3.1 Training**

1599 All research team members will perform the responsibilities as outlined by the delegation of authority  
1600 log. Human Subjects Training and HIPAA training will occur as required by Stanford Policy. Additionally,  
1601 all team members will receive a copy of this document, the Lab Policy Manual, and will be trained  
1602 directly by PI [name] on the purpose of the project and their responsibilities. Research staff will be trained  
1603 on Informed Consent, Phone Screening, and Case Report Form Completion by the PI and other senior  
1604 lab research staff. The latter will monitor appropriate conduct and form completion on an ongoing  
1605 basis, in collaboration with the lab manager (to be hired soon) and the PI ([name]). Research team  
1606 meetings will occur frequently with the PI to ensure ongoing understanding by project staff and to  
1607 address any concerns.

1608 *Regulatory and Ethical Training Requirements*

1609 The lab manager and the IRB manager will ensure that all research personnel have completed required  
1610 federal and institutional training, and will maintain documentation of such. The managers will schedule  
1611 annual training workshops, development of training agendas, and preparation of materials to reinforce  
1612 ethical research and Good Clinical Practices. Outside speakers, such as those from the IRB, Stanford  
1613 Bioethics Consultation Service, and Spectrum will be invited for training workshops.

- 1614
  - Human Subjects Protections: Training will include guidelines related to: HIPAA regulations and
  - 1615 participant confidentiality, ethical research conduct, and human subject interactions.
  - 1616 • Conflict of Interest: Compliance with Stanford's conflict of interest policies and ongoing
  - 1617 monitoring will also be maintained by the managers and the PI.

1618 **10.3.2 Quality Control Committee**

1619 All consent forms and CRF's will be monitored by both the research and the IRB manager. Monitoring  
1620 results will be provided to the DSMB and the research team at quarterly research meetings.

1621 **10.3.3 Metrics**

1622 The metric for the primary outcome measure is self-reported pain. Daily Android data and participant  
1623 questionnaires will be reviewed by the research team on a regular basis, minimally at the Baseline and  
1624 Post-treatment Visits and at least once during the treatment course. The managers and the PI will also  
1625 perform quality assurance by reviewing these materials on a quarterly basis.

1626 10.3.4 Protocol Deviations

1627 A major protocol deviation or violation includes any procedure that differs from the IRB approved  
1628 protocol that was intended to eliminate an immediate hazard to the participant, was harmful, or is  
1629 possible serious or continued non-compliance by a research team member.

1630 Major protocol deviations will be communicated to the PI immediately. All events will be communicated  
1631 to NCCIH within five days of the PI learning of the event. A description of the event will be included. The  
1632 IRB manager will also submit this information to the IRB.

1633 All minor protocol deviations (those that do not meet the definition of a major deviation and do not  
1634 affect the interpretation or outcome of the project) will be reported to NCCIH and Stanford IRB annually.

1635 For each participant, a Protocol Deviations Log will be maintained in the participant's data binder. A  
1636 comprehensive Protocol Deviations Log will be maintained by the research assistant.

1637 10.3.5 Monitoring

1638 *Trial Monitoring*

1639 Adverse Events, Serious Adverse Events, Unanticipated Problems, and Protocol Deviations will be  
1640 monitored on a continual basis and reported per information in the relevant sections. Specifically, QA  
1641 monitoring will occur once a month at the first Monday of the month, by the research team who will  
1642 complete a QA monitoring CRF on REDCAP for each participant. Documents/CRF QA's will include:  
1643 consent forms, patient surveys, research team CRF's, and acupuncturist's CRF's and audios. All AE's,  
1644 SAE's, UP's, and PD's will be logged in separate Excel Spreadsheet for study participants. To ensure that  
1645 we do not miss any items, a QA monitoring CRF is created on REDCAP for each participant and will be  
1646 filled out monthly.

1647 Additional ongoing monitoring will occur as detailed below. Results will be recorded on a monitoring  
1648 log. The PI will review and sign-off on the results and any suggested resolutions.

1649 The consent forms of the first 10 participants will be reviewed for accuracy and completion immediately  
1650 after enrollment. Subsequently, consent forms will be reviewed for completion every 3 months.

1651 The case report forms for the first four sessions completed by *each* provider will be reviewed  
1652 immediately after the visits (within one day) for completeness and accuracy. Subsequently CRFs from  
1653 15-20% of each acupuncturist's sessions will be reviewed every 4 months.

1654 The audio recordings for the first four sessions completed by *each* provider will be reviewed  
1655 immediately after the visits (within one day) for protocol adherence. Subsequently recordings from 10-  
1656 20% of each acupuncturist's sessions will be reviewed every 3 months (using the Ceiling function). We  
1657 will review these recordings to examine adherence to communication guidelines between the provider  
1658 and the participants and to protocols for intensity of the needle stimulations.

1659 The results of the monitoring will be reported at quarterly research meetings for the project.

1660 *Case Report Form Completion*

1661 Data discrepancies will be compared to any source data and corrections made by drawing a single line  
1662 through the original value, providing the correct value, dating, initialing, and providing a reason for the

1663 correction (corrections can be made this way in REDCap). Missing data or data discrepancies that cannot  
1664 be resolved by verifying source data will be left as missing. The PI will be the primary person reviewing  
1665 these data. For acupuncturist's procedure notes which are standardized, the PI may train the research  
1666 assistant to review these data.

